#### Key secondary endpoints

Key secondary endpoints include the individual components of the primary endpoint such ability to wash themselves, 4 m walking ability during the 30‐day intervention phase, and the PGA at day 30. Furthermore, key secondary endpoints include also change in the quality‐of‐life score using the ‘overall quality of life’ scale (i.e. question 15) of the EORTC QLQ‐C15‐PAL questionnaire (European Organization for Research and Treatment of Cancer Quality of Life Questionnaire‐Core 15‐Palliative Care^21^) as well as change in NT‐proBNP during the 30‐day intervention phase.

#### Other secondary endpoints

Other secondary endpoints are the change in 4‐m walking time (with a minimum difference of 0.3 s to declare superiority) during the 30‐day intervention phase, the PGA at time points other than day 30, changes in Eastern Cooperative Oncology Group (ECOG) Performance Status,^29^ Karnofsky Performance Status,^30^ and further questionnaire‐based quality‐of‐life assessments (i.e. the EORTC QLQ‐C15‐PAL functioning scales [physical, emotional]), and symptom scales [pain, fatigue, nausea/vomiting, lack of appetite, dyspnoea, constipation, sleeping difficulties]; Palliative Performance Scale [PPS], Palliative Prognostic Index [PPI], and Palliative Prognostic Score [PaP]). We also will analyse changes in LVEF (site reported) and estimated glomerular filtration rate (eGFR) over time (i.e. during the intervention phase). The ECOG scales categorize functional impairment into six grades: fully active (0), restricted in physically strenuous activity (1), ambulatory and capable of all selfcare, but unable to carry out any work activities (2), limited selfcare; confined to bed or chair more than 50% of waking hours (3), completely disabled – totally confined to bed or chair (4), and dead (5). The Karnofsky scale complements this by scoring functional status on a scale from 100 (normal function, no symptoms) to 0 (death), with intermediate scores reflecting varying degrees of self‐care dependency and disability.

All endpoints (primary, key secondary, and other secondary endpoints) will be assessed in the intervention phase (day 1–30) and in the open‐label extension phase (day 31–60), and, thus, over the whole study period from baseline to day 60.

### Tertiary endpoints

Tertiary endpoints include additional outcomes derived from echocardiographic data analysed by the central echo core laboratory. In addition to standard transthoracic echocardiography (TTE) performed by local investigators in accordance with current European Society of Cardiology recommendations at screening, baseline (with the screening echocardiogram serving as the baseline assessment), and on days 30 and 60, anonymized images will be centrally analysed at the Cardiovascular Imaging Laboratory of the West German Heart and Vascular Center. Parameters assessed will include LVEF (biplane method), E/A ratio, E/e' ratio, left atrial volume, LV muscle mass, LV end‐diastolic diameter, and presence of high‐grade valvular heart disease. In patients managed in ambulatory care, echocardiography will be performed using mobile devices.

#### Safety endpoints

Safety endpoints include all‐cause mortality during 30 days (end of intervention phase) and 60 days (end of extension phase) as well as until the end of follow‐up for survival of all patients (i.e. 30 days after the last study visit of the last patient). Other safety endpoints include monitoring adverse events such as acute kidney injury, hyperkalaemia, and symptomatic hypovolaemia and hypotension. Detailed descriptions of secondary and safety endpoints are provided in *Table* *3* and online supplementary *Appendix*
*S1*.

**Table 3 ejhf3799-tbl-0003:** Endpoints of the EMPATICC trial

**Primary endpoint (assessed in the controlled treatment phase)**
Win ratio hierarchical endpoint:
Days alive and able to wash themselves since baseline during 30 days of follow‐up to the end of the placebo‐controlled phase, with counts ranging from 0 to 32 days.^a^, ^b^
*Note 1: Definition of ‘washing themselves’: patient performed act of washing by themselves without interference of staff, regardless of whether as shower or bath, on a sink, or using a ‘sponge bath’ in the bed*.
*Note 2: Higher number of days (or proportion of days) will be counted as win, if the difference is >1 day (or a equivalent proportion)*.
2 Number of days alive and able to walk 4 m, assessed up to three times (days 10, 20, and 30), with counts ranging from 0 to 3 days.
*Note 1: Walking ability and time are assessed starting in a still standing position – timing starts with the first foot movement and ends when one foot completely crosses the 4 m‐finishing line. Times are used to calculate walking speed (see also other secondary endpoints). If a patient has not completed the 4 m walking distance within 60 s, the patient is considered not being able to walk 4 m and the related speed is set at zero*.
*Note 2: Higher number of days will be counted as win*.
3 PGA of well‐being during the 30‐day period to the end of the placebo‐controlled phase (7‐point Likert scale).
*Note: Better PGA score counts as win, but only if the winning score is better than ‘much worse’*.
**Key secondary endpoints (assessed in the controlled treatment phase)**
Individual components of primary endpoint in the controlled treatment phase
Change in ‘overall quality of life’ scale using the EORTC QLQ‐C15‐PAL questionnaire from baseline to day 30
Change in NT‐proBNP from baseline to day 30
**Other secondary endpoints**
Change in 4 m walking time
PGA at time points other than day 30
Change in ECOG Performance Status
Change in Karnofsky Performance Status
Change in QoL and overall status – assessed using the following questionnaires:
∘ EORTC QLQ‐C15‐PAL functioning scales (physical, emotional), and symptom scales (pain, fatigue, nausea/vomiting, lack of appetite, dyspnoea, constipation, sleeping difficulties)
∘ PPS
∘ PPI
∘ PaP
Change in LVEF
Change in eGFR
All these endpoints (primary, key secondary, and other secondary endpoints) will be assessed in the intervention phase (day 1–30 [±2]).
**Safety endpoints**
AEs
All‐cause mortality
Reported SAEs, including but not limited to:
∘ Acute kidney injury
∘ Hyperkalaemia
∘ Hypoglycaemia
∘ Symptomatic hypovolaemia and hypotension
**Subgroup analyses**
Outcomes will be analysed across subgroups based on:
Sex
Age
Baseline functional status (self‐care, mobility, 4 m walking time)
Body mass index
Tumor type:
∘ Gastrointestinal
∘ Hepatopancreatic biliary
∘ Lung
∘ Urogenital
∘ Other
**Tertiary endpoints and additional analyses**
LVEF (biplane method)
E/A ratio
E/e' ratio
LA volume
LV muscle mass
LV end‐diastolic diameter
Presence of high‐grade valvular heart disease
In addition, all above endpoints, safety assessment and subgroup analyses will also be assessed in the open‐label extension phase (day 31–60), and over the whole study period from baseline to day 60 (as tertiary endpoints).

AE, adverse event; ECOG, Eastern Cooperative Oncology Group; eGFR, estimated glomerular filtration rate; EORTC QLQ‐C15‐PAL, European Organization for Research and Treatment of Cancer Quality of Life Questionnaire‐Core 15‐Palliative Care; LV, left ventricular; LVEF, left ventricular ejection fraction; NT‐proBNP, N‐terminal pro‐B‐type natriuretic peptide; PaP, Palliative Prognostic Score; PGA, patient global assessment; PPI, Palliative Prognostic Index; PPS, Palliative Performance Scale; QoL, quality of life; SAE, serious adverse event.

^a^
If both patients complete the phase, the shorter follow‐up time is considered; if only one completes, the specific follow‐up time is used; if neither completes, day 30 is imputed.

^b^
Withdrawal cases will depend on whether the withdrawal is independent of or dependent on disease severity.

#### Subgroup analyses

Subgroup analyses will explore variations in outcomes based on sex, age, baseline self‐care/mobility status/4‐m walking time, body mass index, and tumour type (gastrointestinal, hepatopancreatic biliary, lung, urogenital, or other).

### Sample size calculation

This study aims to randomize a minimum of 72 patients who would complete the trial, with 36 patients each in the intervention and control groups. The sample size calculation is based on a two‐sided alpha level of 0.05 and a power of 85%. Assuming the number of days alive and able to wash themselves during the last 4 weeks is 11 ± 6 days (mean ± standard deviation) in the control group, the intervention is expected to improve this measure by 5 days during the 28‐day treatment period. To account for an estimated 20% dropout rate, the study anticipates retaining data from 58 patients. Power analysis, conducted using the Wilcoxon rank‐sum test at a two‐sided alpha level of 0.05, confirms 85% power for 72 enrolled and 58 completing participants (G*Power, version 3.1.9.7). Using other software packages, the power of the study under the same conditions will be 83.4% (nQuery) or 86.4% (SAS). A mean difference of 5 days and a standard deviation of 6 days results in a probabilistic index (i.e. the probability that the days alive and able to wash themselves are larger for a patient in the experimental group as compared to a patient in the control group) of 0.278. A probabilistic index of 0.278 indicates the likelihood that a patient in the intervention group will have more days alive and be able to independently wash themselves than a patient in the control group. If the intervention group achieves at least a 6‐day improvement during the treatment period of 28 days, the power of primary endpoint exceeds 90%. It should be noted that precise power calculations for this study are limited by the very restricted availability of prior data regarding test reproducibility and expected treatment effects. Of note, to account for patient dropouts during the initial 30‐day randomization phase, the protocol allowed recruitment of up to 108 patients. The final sample size was 93 randomized patients. Of note, a sample size of 46 patients per group yields a power of 80% at a two‐sided significance level of 5% given a win ratio of 2.1 and a proportion of bindings of 10%.

### Minimization of bias

The trial employs a double‐blind, randomized design to minimize bias. Except for the unblinded personnel responsible for administering optimized therapy or placebo, all other trial personnel remain blinded until study completion and final data review. Treatment assignments are strictly confidential and accessible only to authorized personnel. Sealed allocation codes are prepared in duplicate for each patient, with one set stored at each site and another maintained by the sponsor for emergency unblinding. Emergency unblinding is permitted only if knowledge of treatment allocation is critical for patient care. In such cases, investigators must document the time, date, reason, and personnel involved in the unblinding. To further maintain blinding integrity, placebo treatments (i.e. pills with colours or saline infusions) are designed to mimic the intervention. Standardized procedures, such as using opaque infusion wraps and black tubing for intravenous administration, ensure the indistinguishability of active and placebo treatments. Treatment compliance will not be formally assessed, but ‘adherence days’ per study phase (intervention phase, extension phase) will be determined from administered and untaken medication records. Before data release for statistical analysis, a blinded review will identify protocol deviations that may potentially affect results, including a percentage of adherence days of <80% of the individual maximum, which will lead to exclusion from the per‐protocol analysis set. This rigorous design minimizes bias and maintains the trial's scientific validity.

### Statistical analysis

Descriptive statistics will summarize qualitative categorical variables with count and percentage and quantitative variables with mean, standard deviation, median, quartiles, and range. Before statistical analysis, a blinded data review will be conducted to identify protocol deviations that may affect study outcomes. Protocol deviations, potential outliers, and missing data will be evaluated following the International Conference on Harmonization (ICH) E9 guidelines.^31^ The primary endpoint will be tested two‐sided at a significance level of 0.05, focusing on a hierarchical composite outcome: stage 1 (days alive and able to wash themselves since baseline), stage 2 (number of days alive and able to walk 4 m), and stage 3 (PGA of well‐being).

Key secondary endpoints will only be tested if the primary hypothesis is rejected, with multiplicity adjustment for the five key secondary endpoints performed hierarchically: first, the ‘washing days’ endpoint will be tested at 5% significance, and if rejected, the additional four key secondary endpoints (number of days alive and being able to walk 4 m, PGA of well‐being, overall quality of life [EORTC QLQ‐C15‐PAL question 15], and NT‐proBNP during the 30‐day intervention phase) will be tested using the Hochberg procedure^32^ at 5% significance to control the familywise Type I error rate. All other endpoints will be tested at a nominal two‐sided significance level of 5%. Deceased patients or patients who withdrew from the study (dependent on/independent of disease severity) will be imputed in the analysis. Primary approach taken in the analysis for longitudinal data with follow‐up truncated by death is unconditional; for example, a deceased patient is assigned a worst‐case value (e.g. a PGA value of 8, a walking speed of 0, an ECOG value of 5, a Karnofsky index of 0, and a PPS of 0) or the last observation is carried forward, respectively, if imputation is required.

The primary endpoint analysis for comparison of both treatment groups will employ the win ratio approach, without stratification.^33^, ^34^ Test statistics (Finkelstein–Schoenfeld), *p*‐values, point estimates (win ratio, win difference, win odds), and 95% confidence intervals (CI) will be calculated as specified. Secondary endpoint analyses will include the win ratio approach for ‘days alive and being able to wash themselves since baseline’, with specific win criteria for aggregated washing ability data based on common study visits. The 4 m walking ability will be analysed using a proportional odds logistic regression model at day 30, with patients who died or withdrew considered unable to walk. This model will assess the accumulated frequencies of being able to walk 4 m at 10, 20, and 30 days of follow‐up, with possible outcomes ranging from 0 to 3. PGA of well‐being will be analysed using a mixed‐effects proportional odds model with treatment, visit, treatment‐by‐visit interaction and study centre as fixed effects. Missing self‐reported PGA for deceased patients will be considered as an additional category. Odds ratio with 95% CI will be calculated at time points 10, 20, and 30 days, respectively. Overall quality of life (i.e. question 15) of the EORTC QLQ‐C15 PAL questionnaire and NT‐proBNP will be analysed using Gaussian mixed linear models for repeated measures (MMRM), fitting assessments at 10, 20, and 30 days with fixed effects for group, time, group‐by‐time interaction, baseline, and study centre, assuming a multivariate normal distribution with unstructured covariance for error terms. NT‐proBNP analyses will be on the log‐scale. Least squares means for the intervention group as well as for the difference between treatment groups will be reported with 95% CI. Data from validated scales such as ECOG Performance Status,^29^ Karnofsky Performance Status,^30^ and quality‐of‐life questionnaires^35^ will be summarized by treatment group and time point. Continuous variables (e.g. 4 m‐walking time, Karnofsky Performance Status, PPS, PPI, PaP, LVEF, eGFR) will also be analysed over time based on MMRM. Ordinal variables such as ECOG Performance Status, and PGA score at day 10 and day 20 will be analysed using proportional odds models. Safety endpoints will include adverse events classified by treatment arm. Descriptive summaries will consist of the number of subjects, percentage, and total events categorized by MedDRA system organ class and preferred term. Treatment‐emergent adverse events will be further analysed with a focus on events potentially linked to the intervention, including acute kidney injury, and symptomatic hypovolaemia and hypotension. All endpoints will be assessed in the intervention phase (day 1–30) and separately in the open‐label extension phase (day 31–60), as well as over the entire study period from baseline to day 60.

Cox‐proportional hazards regression model will be used to analyse all‐cause mortality. Kaplan–Meier curves with log‐rank test for group comparisons will also be computed. A hazard ratio with 95% CI will be estimated. The proportional hazards assumption will be visually checked using graphical diagnostics, including scaled Schoenfeld residuals, and by testing the time × treatment interaction. Covariates for multiple regression will include age, sex, body mass index, tumour aetiology, clinical status (ECOG, Karnofsky index, self‐care ability), presence of comorbidities (type 2 diabetes, anaemia, iron deficiency), study centre, screening NT‐proBNP level, and prior cardiovascular therapy. Measurements from TTE of local investigators and central study core lab will compared by the Bland–Altman method. The influence of dynamic allocation will be investigated using re‐randomization tests or by adding variables used in the minimization approach as fixed effects (i.e. age, sex, body mass index, tumour aetiology, clinical status [ECOG, Karnofsky index, self‐care ability], presence of comorbidities [type 2 diabetes, anaemia, iron deficiency], screening NT‐proBNP level and prior cardiovascular therapy); if convergence issues arise, variables will be dropped in order of increasing importance.

Sensitivity analyses will evaluate the robustness of results for missing data, and exploratory analyses may provide insights into ancillary objectives. All statistical calculations will be done in R (R Core Team. R: A Language and Environment for Statistical Computing, R Foundation for Statistical Computing, Vienna, Austria), SAS (SAS Institute Inc., Cary, NC, USA), SPSS (IBM Corp., Armonk, NY, USA) and Stata (StataCorp LLC, College Station, TX, USA).

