### Study visits and follow‐up

Eligible patients will be randomized in a 1:1 ratio to one of two treatment groups: with standardized scheme of HF care including up to four different drugs or standard of care. Randomization will occur on day 1, marking the start of the 30‐day randomized phase. Patients will undergo in‐person assessments on days 10, 20, and 30 (*Table* *2*). Following this, all participants will transition into a 30‐day open‐label extension phase to receive optimized HF therapy. Assessments in the extension phase will be conducted on days 40, 50, and 60 (*Table* *2*). Study discontinuation may occur due to safety concerns, including clinical abnormalities or significant adverse events, such as allergic reactions or diabetic ketoacidosis. All patients are informed at the beginning of the study about the potential for reassessments during the trial. This approach ensures rigorous follow‐up and comprehensive monitoring throughout the study period. The trial will conclude with a final assessment at day 60 or earlier if discontinuation occurs.

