### Primary endpoint

The primary efficacy objective of this study is to assess the impact of optimized HF therapy on self‐care ability and self‐reported health status in terminal cancer patients receiving palliative care. The primary hierarchical endpoint (to be analysed by the win ratio) has the following components: (1) days alive and being able to wash themselves, (2) the ability to walk 4 m, and (3) the self‐reported patient global assessment (PGA) of subjective well‐being during 30‐day period to the end of placebo‐controlled phase.

For the first component ‘days alive and being able to wash themselves’, any method for washing (shower, bath, sink, or sponge bath in bed) will be considered during the 30‐day period to the end of the placebo‐controlled phase (up to the visit of day 30 [30 ± 2 days after the baseline visit]), with the counts ranging from 0 to 32 days. A higher number (or higher proportion) of days will determine the ‘win’, if the difference between two patients being compared exceeds 1 day (or an equivalent proportion). For cases when both patients survive the entire placebo‐controlled phase, then only the period of time of the patient with shorter observation time will be considered (i.e. day 28–32 or the related visit). If only one of the two patients compared reached the final assessment day and the withdrawal of the second patient is considered independent of disease severity (in blinded assessment), the shared observation time (i.e. to the end of study for the patient with shorter observation time) is considered. If only one of the two patients compared reached the final assessment day and the withdrawal of the second patient is considered dependent on disease severity, this person is considered unable to wash themselves, to not being able to walk, and to consider their health ‘much worse’ in PGA until the end of study (i.e. the visit on day 30).

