If neither of the patients complete their study period (due disease progression [i.e. entering the dying process] or death), an imputed observation time (day 30) will be used to assess the outcome for both patients. For patients with documented disease progression related study withdrawal, a worst‐case imputation will be performed, i.e. patients will be considered unable to wash themselves, unable to walk, or considered their health ‘much worse’ in the PGA. If precise day‐by‐day recorded data are not available for both patients, and results for the observation period are only provided as summary statistics at visit‐day 10, visit‐day 20, and visit‐day 30, then results will be calculated up to the end of their last common visit on day 10, 20, or 30, respectively, using the ‘last common visit’ approach. Under the ‘last common visit’ approach, the win criterion for the percentage of days alive and able to wash oneself is defined as a difference between two patients of >15.00% for an observation period extending to visit‐day 10, >10.00% for visit‐day 20, or >5.00% for visit‐day 30, with the patient demonstrating the higher percentage deemed the winner.

The second endpoint component, i.e. the ‘ability to walk 4 m’ (during 30‐day intervention phase), will be assessed at days 10, 20, and 30, with counts ranging from 0 to 3 visits. The patient with a higher number will be the ‘winner’. The walking ability is measured by the time taken to walk 4 m, with timing starting from the first foot movement and ending when one foot crosses the finishing line. The result is also used to calculate walking speed. For patients who die or are unable to walk, the walking speed will be recorded as zero.

The third component of the primary endpoint, i.e. ‘self‐reported PGA of subjective well‐being’, will be assessed at the last common assessment visit where both patients were alive (i.e. day 30, 20, or 10). The PGA assesses overall well‐being since enrolment on a 7‐point Likert scale ranging from ‘much worse’ to ‘much improved’. For patients who died, a value (8) ‘dead’ will be assigned. A better PGA score will be considered a ‘win’ but only if it is better than at least score of 6 (i.e. a patient needs to at least ‘moderately worse’). Pre‐specified sensitivity analyses for this win ratio include introducing all‐cause mortality as the highest‐priority component, where longer survival wins with a difference exceeding one day, and reversing the order of walking and PGA components.

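### Withdrawals are scored by rules that disagree between the primary endpoint and its walking key secondary, and adverse-event withdrawals are assigned to no class

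*Protocol article*

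**What the plan says.** The Primary endpoint section describes a pair in which one patient completes and the other withdraws. If "the withdrawal of the second patient is considered independent of disease severity (in blinded assessment), the shared observation time" is what counts, the comparison stops when the shorter follow-up stops. If the withdrawal depends on disease severity, "this person is considered unable to wash themselves, to not being able to walk", with the worst PGA category as well, until the day 30 visit. Footnote b of Table 3 repeats the split.

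The same section then gives three further rules:

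- If neither patient completes, because of progression or death, "an imputed observation time (day 30) will be used to assess the outcome for both patients".
- Worst-case imputation is specified "For patients with documented disease progression related study withdrawal".
- Walking (stage 2) is scored "with counts ranging from 0 to 3 visits. The patient with a higher number will be the ‘winner", with no mention of common visits. PGA (stage 3) is explicitly taken at the last assessment that both patients share.

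The Statistical analysis section states that patients who died, and withdrawals of both kinds, are imputed by worst case or by last observation carried forward. It does not say which method goes with which class of withdrawal. For the walking key secondary, a proportional odds model of the 0-to-3 count, it specifies "with patients who died or withdrew considered unable to walk". Table 3 lists this endpoint as an individual component of the primary, and it sits in the Hochberg family.

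Study visits and follow-up foresees discontinuation for safety concerns, including "significant adverse events, such as allergic reactions or diabetic ketoacidosis". No section assigns these cases to either withdrawal class.

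**The concern.** One patient can be handled differently by analyses of what is presented as the same outcome. A withdrawal judged independent of disease severity is neutral for washing, of uncertain status for the walking stage, and a failure in the walking key secondary. A difference between the primary result and its own component could then come from the scoring rule and not from the treatment.

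The second issue is the criterion for the split. It asks only whether a withdrawal depends on disease severity, not whether the treatment caused it. An assessor who applies it literally, and blinded, may class an allergic reaction or ketoacidosis as independent. The patient's days up to withdrawal are kept and the rest are dropped. If such withdrawals are commoner on active treatment, part of the harm does not reach the primary comparison.

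**Working it through.** **1. The plan's own figures.** No stated figure is in dispute here, and they reproduce. Inputs from Sample size calculation: difference 5 days, SD 6, 58 completers (29 per arm), two-sided 0.05.

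- Noether: p = Φ(5/(6√2)) = 0.722. Power = Φ(√(12 × 58 × 0.25) × (0.722 − 0.5) − 1.96) = 0.834, the stated nQuery value of 83.4%.
- Noncentral t with efficiency 3/π: 86.1%, against the stated 85% and 86.4%.
- Win-ratio statement (2.1, ties 10%): σ² = 4 × 1.10/(3 × 0.25 × 0.90) = 6.52. N = 6.52 × (1.96 + 0.84)²/(ln 2.1)² ≈ 93. At 92 patients power is 79.6%, against the stated 80%.

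**2. The rules side by side.**

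| Analysis | Withdrawal dependent on severity | Independent of severity | Adverse event |
|---|---|---|---|
| Stage 1, washing | worst case to day 30 | shared time | not assigned |
| Stage 2, walking | worst case | not stated for the 0-to-3 count | not assigned |
| Stage 3, PGA | worst category | last common visit | not assigned |
| Walking key secondary | unable | unable | unable |
| General imputation statement | worst case or LOCF, not allocated | worst case or LOCF, not allocated | not mentioned |

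Pairs in which neither patient completes and one withdrew independently of severity also have no rule, because the day 30 rule is worded for progression or death.

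**3. A worked pair.** Patient A walks at day 10 and withdraws on day 12 for a reason judged independent. Patient B completes and walks at all three visits. Suppose that washing is tied over the shared 12 days, so that stage 2 decides.

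- Stage 2 with the shared-time limit: 1 v 1, a tie.
- Stage 2 read literally: 1 v 3, A loses.
- Walking key secondary: A scores 1 of 3, B scores 3 of 3.

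On the first reading the primary and its component disagree. On the second, stages 1 and 2 of the primary disagree.

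**4. What the classification of adverse-event withdrawals could change.** This is a simulation of stage 1 only.

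- From the documents: control mean 11 days, active mean 11 or 16, SD 6, 46 per arm, win margin of 1 day scaled to the time compared.
- Assumed: beta-binomial washing days with a constant daily probability per patient, no deaths, and a fraction f of the active arm only withdrawing on a uniformly distributed day from 3 to 20.
- Analysis: Finkelstein–Schoenfeld test, 3,000 trials per row.
- Shared time compares counts up to the earlier exit. Worst case keeps the days before withdrawal and counts every later day as unable.

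| Active mean | f | WR, shared | WR, worst case | Significant benefit, shared / worst | Significant harm, shared / worst |
|---|---|---|---|---|---|
| 11 (no effect) | 0% | 0.99 | 0.99 | 2.2% / 2.2% | 2.6% / 2.6% |
| 11 | 5% | 0.99 | 0.92 | 2.2% / 1.1% | 2.7% / 5.1% |
| 11 | 10% | 0.99 | 0.85 | 2.2% / 0.5% | 2.7% / 8.5% |
| 11 | 20% | 0.99 | 0.73 | 2.1% / 0.0% | 2.7% / 21.1% |
| 16 (planned) | 0% | 2.91 | 2.91 | 97.1% / 97.1% | 0 / 0 |
| 16 | 5% | 2.89 | 2.56 | 97.1% / 93.2% | 0 / 0 |
| 16 | 10% | 2.87 | 2.27 | 97.2% / 84.5% | 0 / 0 |
| 16 | 20% | 2.83 | 1.81 | 97.0% / 58.3% | 0 / 0 |

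The Monte Carlo standard error is at most √(0.583 × 0.417/3000) = 0.9 percentage points. The base value of 2.91 follows from the 5-day planning effect and is not the plan's 2.1. The table should be read for the contrast between rules.

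**The case against.** Several arguments on the other side have weight.

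- *Adverse-event withdrawals are not placed in the independent class.* This is correct. A reader might infer that the plan puts drug-intolerance withdrawals there, but no section does. The decision is made case by case under blinding, and its criteria may well be in the full protocol. The documents also do not say that such events arise mainly from the active drugs, although the Statistical analysis section does single out kidney injury, hypovolaemia and hypotension for their possible link to treatment. What stands is that the only criterion given is disease severity, and worst case is tied to progression. Blinding prevents deliberate steering; it does not add treatment causation to the criterion.
- *Shared time may govern the whole pair.* This is a fair reading, because the severity-dependent half of the rule expressly covers all three components. A certain loss at stage 2 therefore cannot be asserted. But the shared-time sentence sits under washing, and PGA has its own common-visit limit while walking has none. Adopting this reading also leaves the conflict with the key secondary.
- *The walking model is a different analysis.* Shared time is a pairwise device, and a per-patient model cannot use it directly. Scoring every withdrawal as unable is a legitimate rule, and the general imputation statement is compatible with it. It is nevertheless a different rule for an outcome presented as the primary's own component.
- *The shared-time rule does not favour a treatment without effect.* This stands: the win ratio is 0.99 at every rate in the table. The gap between the rules is a choice of what to estimate, and worst case after an adverse event is itself an assumption.
- *Size.* A reader might start from the plan's 2.1 with 10% ties (wins 0.9 × 2.1/3.1 = 0.610, losses 0.290) and score a fraction f as losses: 0.610(1 − f)/(0.290(1 − f) + f) = 1.78, 1.52 and 1.31 at 5, 10 and 15%. That overstates the effect, because it makes each withdrawn patient lose every pair, although washing days before withdrawal are kept.

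The plan also has mortality and adverse events by arm, a mortality-first win ratio, general missing-data sensitivity analyses and an expectation of low attrition. These lessen the risk but do not decide the rule.

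**Conclusion.** The point holds as a conflict and a gap in the withdrawal rules. The conflict between the primary's reason-dependent rule and the reason-blind rule of the walking key secondary is plain in the text. Stage 2 is ambiguous. Adverse-event withdrawals are unclassified, and a literal use of the severity criterion can remove the days after a treatment-caused withdrawal from the primary comparison. The consequence is masked harm, not manufactured benefit.

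At the planned effect, moving such withdrawals from shared time to worst case lowers the simulated stage-1 win ratio by about 11% (2.89 to 2.56), 21% (2.87 to 2.27) and 36% (2.83 to 1.81) at 5, 10 and 20% withdrawal. With no other effect and 20% withdrawing, the chance of a significant signal of harm is 2.7% under shared time and 21.1% under worst case.

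These sizes rest on withdrawals confined to the active arm at assumed rates. The plan budgets 20% dropout overall and does not count deaths as dropouts, but it gives no figure by reason or arm. With few such withdrawals, or with similar numbers in both arms, the masking would be smaller. The inconsistency between the rules would remain.

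**What to change.** 1. State that stage 2 is limited to common visits when a withdrawal is independent of both disease severity and treatment. State the same for pairs in which neither patient completes.
2. In the blinded review already planned, classify withdrawals for adverse events, intolerance or safety explicitly as not independent. Use any data recorded after withdrawal; otherwise score them like severity-dependent withdrawals. Report the shared-time scoring as a sensitivity analysis.
3. Use the same classes in the walking key secondary, with a stated method for the missing visits of independent withdrawals, such as multiple imputation of the 0-to-3 count or a win-ratio comparison over common visits. Keep the rule that every withdrawal is unable to walk as a sensitivity analysis.
4. In the general imputation statement, say which class receives worst case and which receives last observation carried forward.

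The cost is revised analysis wording and one more classification in the blinded review. The estimate may become slightly less favourable to the intervention. The article says that the trial ended on 30 January 2025. If the data are already unblinded, the primary rule should not be changed, and the alternative scorings can only be reported as sensitivity analyses.
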